## Methods

### Participant recruitment

Advertisements inviting healthy participants to participate will be widely placed. Areas will include physical notice boards, table display, electronic notice boards, the intranet/internet of local universities and colleges (with permission), social media, the local press, television and radio. Staff from the MLW team will be permitted to participate providing they are not members of the study team.

Interested persons will be asked to contact the research team by phone, email or text for further information. Once potential participants who are interested have contacted the research team, they will then be invited to meet a member of the research team. The research team will explain the study at the meeting and the Participant Information Sheet will be provided. Participants will then consider if they wish to continue (see
Figure 1).

At visit 1, the informed consent process will be conducted by either the research nurse or research doctors who are formally delegated by the Chief Investigator, trained in GCP, consent and the trial protocol. The following consent, inclusion and exclusion criteria will be applied as below.

### Inclusion criteria

Adults aged 18–40 years - ages chosen to minimise the risk of pneumococcal infectionFluent spoken and written Chichewa or English - to ensure a comprehensive understanding of the research project, their proposed involvement and communication with all members of the research team

### Exclusion criteria

Previous pneumococcal vaccinationHIV-infection: HIV testing will be performed by trained personnel certified in HIV Testing Services (HTS). “Determine” or “Unigold” will be used as the first line tests. Any participants identified as HIV-infection positive will be referred to the governmental system for infection confirmation, treatment and follow up.Close physical contact (e.g. sleeping in the same room or nursing) with at risk individuals (children under 5 years age, immunosuppressed adults, elderly, chronic ill health)Allergy to penicillin/amoxicillinAcute illness○ Current illness○ Acute illness within 3 days prior to inoculation○ Antibiotic treatment within 2 weeks of inoculation

Chronic illness that may impair immune response or impair ability to comply with study procedures and safety monitoring (e.g. HIV, diabetes).Taking immunosuppressive medication that may include but are not limited to steroids and steroid nasal spray.Pregnancy - minimise risk of pneumococcal diseaseInvolved in another clinical trial unless observational or in follow-up (non-interventional) phaseHistory of drug or alcohol abuse. This is very difficult to ascertain in a history therefore we will exclude people reporting drinking alcohol more than twice per week.History of Smoking○ Current regular smoker (smokes daily/smokes > 5 cigarettes per week) - minimise risk of pneumococcal disease○ Recent smoker i.e. within the last 6 months - minimise risk of pneumococcal disease○ Ex-smoker with a significant smoking history (>10 pack years) – minimise risk of pneumococcal diseaseUnable to give informed consentIn case of any uncertainty or concern, the PI will take clinical responsibility for the decision.

### Screening and preliminary assessment

Following consent, inclusion and exclusion criteria, data and samples will be collected.

• Clinical examination - the initial clinic visit will include a focused clinical history and targeted clinical examination involving auscultation of the lung fields and heart sounds. Participants will be informed if their clinical examination is normal. Should a previously unrecognised abnormality be identified, this will be explained to the individual, and appropriate investigations and follow-up will then be arranged by the study team. Further participation will be determined at the discretion of the study doctor dependent on the nature of the abnormality detected. If the participant is not eligible due to an acute illness, they may be re-screened at a later date with their verbal consent.

•
*Nasal wash* - will be performed using our published method
^11^. This is a well-used and validated technique to collect nasal bacterial specimens used successfully by the Liverpool CHIM team who will rigorously train the Malawi team. Briefly, 5ml of sterile saline is instilled and held for a few seconds in the nares before being expelled into a sterile Galli pot. This is repeated twice in each naris using 20ml saline in total. In the event of nasal wash loss (defined as cough/sneeze/swallow), the procedure may then be repeated to obtain an adequate specimen. Should the nasal wash reveal natural colonisation of pneumococcus, the participant will continue in the study and receive the inoculation as per protocol, unless the natural serotype is identified as 6B, in which case the patient then leaves the study at day 2. All pneumococcal carriage negative participants will continue in the study.

•
*Nasosorption strips* - Nasosorption will be obtained before a nasal wash and/or inoculation. The strips are like blotting paper developed by Hunts Development Ltd (UK, catalogue number: NSFL-FXI-11). They collect concentrated nasal lining fluid before the nasal wash to measure inflammatory responses induced by infection that may be associated with increased colonisation density and acquisition. Concentrate nasal fluid will be used to measure cytokine levels by multiplex bead array. Blotting paper will be held inside the nostril for up to 3 minutes until soaked, removed and placed in the microcentrifuge tube for storage.

•
*Nasal Cells* – will be collected using a nanosampling method in which cells are obtained through minimally invasive superficial nasal scrape biopsies (rhinoprobe). Work from our Liverpool team demonstrates that participants can be biopsied multiple times with no significant side effects. Nasal cell samples will be obtained after nasal wash samples have been taken. Up to 4 samples (2 per nostril) will be obtained at each nasal sampling visit. If the researcher finds that the sample is insufficient, for example no cells are visible on the rhinoprobe, the sample can be repeated immediately. The rhinoprobes are placed in transport media immediately after collection.

•
*Blood* – blood samples will be obtained using venepuncture by an appropriately trained team member. In the entire duration of the study, a maximum of 100mL of blood will be collected across the entire study for analysis including a full blood count. Participants with an abnormal full blood count will be removed from the study as determined by the clinical team (result day 2).

•
*Throat swabs* – simple posterior pharyngeal swabbing on a dry swab.

•
*Saliva* – salivette held for saturation or a spit in the tube.

•
*Urine Sample* – for a pregnancy test as part of the safety screening. 

### Visit 2 Pneumococcal inoculation

***Preparation of bacterial stock and inoculation***

• Initial preparation and transfer to MLW - Microbiological and sequence confirmation of the purity of the inoculum will take place at LSTM and reference Public Health England laboratories prior to the onset of the study. Once complete, the microbiologically and genetically confirmed
*Streptococcus pneumoniae (S. pneumoniae)* capsular serotype 6B strain BHN418 will be transferred from the LSTM to MLW. Microbiological and serotype confirmation will take place at MLW upon receipt.

• Preparation of bacteria for carriage studies at MLW – LSTM will provide MLW with mid-log broth cultures of pneumococcus for this feasibility study, these will be frozen at -80°C in aliquots of glycerol-enriched media. Immediately prior to participant inoculation, aliquots will be thawed, washed twice, and re-suspended in sterile saline at an appropriate density for each inoculation dose. The LSTM Standard Operating Procedure (SOP) will be used.

• Confirmation of accuracy - Following culture by the laboratory team at MLW, aliquots of the bacterium will be returned to the UK, as a quality control measure, to confirm the identity, purity and penicillin sensitivity of the isolate. These bacterial isolates will be sequenced in the UK to confirm identification.

• Regulatory approval -
*S. pneumoniae* transfer will be reported to the Malawian Pharmacy, Medicines and Poisons Board (PMPB, national regulatory authority) prior to initiation of the feasibility study. PMPB will review the protocol as part of NHSRC, and have advised that the UK Medicines and Health care products Regulatory Authority (MHRA) position on EHPC (not an investigational medicinal product) will be recommended.

***Inoculation***

• Inoculation - using a P200 micropipette, 0.1ml saline containing the desired dose (see
Figure 2) of pneumococcus will be instilled into the nose. The participant will be seated in a semi-recumbent position. After inoculation, the participant will remain in this position for up to 15 mins. They will be given a post-inoculation advice sheet (including emergency contact details), thermometer, a course of amoxicillin (500mg TDS for 3 days) and a daily symptom log to complete.

• Dose escalation and sham inoculation - We have adopted a step-wise approach to escalating the inoculation dose. The protocol is designed to: a) minimise the possibility that we try repeatedly to attain carriage at a dose in which it is unlikely to occur; b) maximise safety by inoculating small groups (in case adverse events occur) before continuing on to larger groups in which we will be able to give reasonable precision to estimate carriage rates. Groups 1, 2 and 3 will receive increasing doses of pneumococcal inoculation as explained in
Figure 2. Briefly, 20,000 cfu/naris (Group 1) is not expected to achieve carriage. If 80,000 cfu/naris achieves more than 4 from 9 participants with carriage, then the study will end at that point. Sham inoculation with 0.9% normal saline has been incorporated into the study design to assess whether any potential observed effects in participants are pneumococcal challenge-related or simply reflect the study conditions. Participants will receive only one inoculation dose. If carriage is not achieved after inoculation, participation will be concluded upon completion of visit eight.

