**Figure 2. f2:**
[figure not shown]
Dose escalation study design, adapted from Waddington
*et al*.
^12^. The doses for Groups 1, 2 and 3 will be 20000, 80000 and 160000 pneumococcal colony forming units (CFU) per naris respectively. All participants will be monitored for adverse effects and for pneumococcal carriage. The first cohort will be inoculated with 20,000 CFU/naris (
**Inoculation A**).
**†**: Eight participants will be randomised 3:1 to pneumococcal inoculation (n=6) or sham inoculation with 0.9% saline (n=2). If ≥2/6 participants from the initial cohort of eight develop experimental pneumococcal carriage, a further 4 participants will be recruited to this dose cohort.
*****: Four participants will be randomised 3:1 to pneumococcal inoculation (n=3) or sham inoculation with 0.9% saline (n=1). If the combined carriage rate of the completed cohorts is ≥4/9 (6+3 nasally challenged with pneumococcus), then the nasal challenge dose will be established, and we will conclude the study. If at either of these decision points, the carriage rate is insufficient, the algorithm will be restarted with a higher challenge dose of 80,000 CFU/naris (
**Inoculation B**) and the recruitment schedule repeated. If at 80,000 CFU, the carriage rate is insufficient, then an additional cohort of participants will be recruited to the 160,000CFU/naris dose escalation group (
**Inoculation C**).
**‡**: 12 participants will be randomised 3:1 to pneumococcal inoculation (n=9) or sham inoculation with 0.9% saline (n=3). We have previously demonstrated 50-60% carriage rates with the 80,000 CFU 6B dose in the Liverpool pneumococcal controlled human infection model
^6,
13^.

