Figure 2 since an alternative participant will be recruited in the case of withdrawal of a participant. Participants missing study visits so that no day 2, 7 or 14 data is available will be withdrawn from the study and their data excluded from data analysis. A new participant will be recruited in such a case and this new participant will be allocated to the same pneumococcus / sham inoculation as the participant ID for the withdrawn participant was randomised to. The primary feasibility endpoint will be assessed, at each of the five analysis time points using colonisation results data from all participants that are required for that stage’s analysis and that have completed visit 7 (d14). Other analyses are primarily descriptive or make use of censored data techniques, so that no advanced missing data methods will be used in these analyses. Data collection forms are provided in extended data
^21^. 

***Statistical significance and multiple testing.*** Success (feasibility) of the study will be decided according to the decision rules stated on
Figure 2.

Success (safety) of the study will decided by decision of the DSMB & TC upon revision of each SAE and SUSAR. For this reason, no formal null hypothesis significance testing will be performed for the main analysis and no multiple testing adjustment will need to be made.

For secondary analyses, statistical significance is defined as p<0.05, but effect sizes / parameter estimates, exact p-values and confidence intervals will be stated. While we will report on statistical significance, results will be presented and discussed in accordance with recent guidance
^22^.

***Technical details.*** All analyses and figures will be performed using the R environment (v.3.5.3 or later) for statistical computing and graphics and associated packages
^23^.

***Feasibility.*** The primary analysis aims to establish feasibility of the Malawi CHIM: does one of the three doses (20,00, 80,000, 160,000 CFU) lead to ≥50% nasal colonisation?

To assess this, the decision algorithm specified in the study design (

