Figure 2) is followed and no statistical analysis is required. However, we will complement this with a number of descriptive and secondary analyses: For each inoculation dose used in the study, we will estimate colonisation (by serotype 6B) rates and compute 95% exact, binomial confidence intervals. We will also compute this for participants inoculated with the sham, saline solution. If more than 1 dose is used in the study, we will plot the estimated colonisation rate against inoculation dose for a crude estimate of the dose-response curve. For each inoculation dose, we will also plot time curves of colonisation rates at visits 0 (d-5), 4 (d2), 6 (d7), 7 (d14). We will also use lytA qPCR to assess nasal carriage by
*Streptococcus penumoniae*. We will repeat all analyses using this method of carriage detection. Further, for the qPCR results, we will estimate average carriage densities and associated 95% confidence intervals for each challenge dose. If more than one dose is used, we will also plot individual carriage densities against inoculation dose for a crude estimate of the carriage density dose response curve. We will estimate the lower limits of detection and quantification for the qPCR data, then use censored data techniques to account for the uncertainty associated with values below these limits.

We will compile a summary table for demographic (age, sex), baseline physiological (pulse rate, oxygen saturation on room air, systolic blood pressure, diastolic blood pressure, tympanic body temperature, height, weights, BMI, baseline carriage of
*S. pneumoniae* other than serotype 6B) and baseline immunological variables. Baseline physiological and immunological variables are those measured at the inoculation visit or for which the sample was taken at the inoculation visit (prior to the inoculation). Analogous tables will be compiled for the assessments made at visits 2–8.

***Safety.*** AEs, SAEs, SUSARs are monitored throughout the study and any decision to stop the trial is taken by the TSC in consultation with the DSMB. At study end, AEs, SAEs and SUSARs will be listed by type and by inoculation group (sham,

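### The Inoculation section gives the 80,000 CFU stopping rule as more than 4 of 9, but the governing Figure 2 rule is at least 4 of 9, and the primary question asks for ≥50%

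*Protocol article*

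**What the plan says.** **Inoculation section (dose escalation paragraph).** The text refers the reader to the figure and then summarises it: "Figure 2. Briefly, 20,000 cfu/naris (Group 1) is not expected to achieve carriage". The next sentence gives the rule for the middle dose: "If 80,000 cfu/naris achieves more than 4 from 9 participants with carriage, then the study will end at that point".

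**Figure 2 legend.** Each of the first two doses starts with six challenged participants. With at least two carriers among the six, three more are challenged. Then: "If the combined carriage rate of the completed cohorts is ≥4/9 (6+3 nasally challenged with pneumococcus), then the nasal challenge dose will be established", and the study concludes. If carriage is insufficient at 20,000 CFU, the same algorithm restarts at 80,000 CFU. For the last step: "If at 80,000 CFU, the carriage rate is insufficient, then an additional cohort of participants will be recruited", at 160,000 CFU.

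**Statistical analysis section.** "Success (feasibility) of the study will be decided according to the decision rules stated on" Figure 2. Under Feasibility, the primary question is whether one of the doses will "lead to ≥50% nasal colonisation". The article continues: "To assess this, the decision algorithm specified in the study design" (Figure 2) "is followed and no statistical analysis is required".

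**Elsewhere.** The Stopping criteria section also ties completion of the study to Figure 2. Study aims (aim 2) and the Study hypothesis both speak of carriage of about 50%, not of a minimum of 50%.

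**The concern.** The Inoculation section and the Figure 2 legend describe the same action at the same dose with the same denominator, and they set different cut-offs: 5/9 or more in one, 4/9 or more in the other. The figure itself is not reproduced in the text at hand, but its legend prints the rule in words, so the missing image does not explain the difference.

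The primary question adds a second mismatch. Out of nine, the smallest count at or above 50% is five. Read as a statement about observed carriage, the question sides with the Inoculation sentence and against the rule that is meant to answer it.

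This threshold is the entire primary decision, since no test stands behind it. It also determines whether more people are challenged: a result treated as insufficient at 80,000 CFU leads to a cohort of 12, nine of them given 160,000 CFU per naris. The misstatement sits in the section that clinical staff would consult for inoculation and escalation. With 4/9 in hand, a reader of that section would not recognise it as the result that ends the study. Settling the cut-off after seeing 4/9 would be a post hoc decision on the primary outcome.

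**Working it through.** **1. The plan's own figure.** The Figure 2 schedule gives a maximum of (8 + 4) + (8 + 4) + 12 = 36 participants. This matches the Recruitment target, so the legend is being read as intended.

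**2. The thresholds as proportions.** 4/9 = 44.4% and 5/9 = 55.6%. No count out of nine gives exactly 50%.

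**3. Which text governs.**

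| Place | Cut-off | Standing |
|---|---|---|
| Inoculation | more than 4/9, i.e. ≥5/9 | brief summary that points to Figure 2 |
| Figure 2 legend | ≥4/9 | the full algorithm |
| Statistical analysis, significance paragraph | none of its own | success decided by Figure 2 |
| Statistical analysis, Feasibility | ≥50% as the question | answered by following Figure 2 |
| Stopping criteria | none of its own | completion defined by Figure 2 |

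Every pointer leads to the legend, so ≥4/9 is operative.

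**4. How often the wordings part.** Let X1 ~ Bin(6, p) and X2 ~ Bin(3, p) be the carriers in the two steps at 80,000 CFU, with the second step opened only if X1 ≥ 2. The cut-offs differ only when X1 + X2 = 4. The paths that pass the first step are (2,2), (3,1) and (4,0), with 15×3 + 20×3 + 15×1 = 120 arrangements. The path (1,3) is excluded because it fails the first step. Hence

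P(exactly 4/9) = 120 p⁴(1 − p)⁵.

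- p = 0.50: 120/512 = 0.2344
- p = 0.55: 0.2026
- p = 0.60: 0.1593

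The range 50–60% is the Liverpool carriage range quoted in the Figure 2 legend.

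**5. Probability that 80,000 CFU is established, given that it is reached.** At p = 0.50, 382 of the 512 equally likely outcomes have four or more carriers. Six of these are the excluded (1,3) path, leaving 376/512 = 0.7344. For five or more, the count is 256/512 = 0.5000, since five carriers always include at least two in the first step.

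| True carriage | ≥4/9 | ≥5/9 |
|---|---|---|
| 30% | 0.2622 | 0.0988 |
| 40% | 0.5054 | 0.2666 |
| 50% | 0.7344 | 0.5000 |
| 60% | 0.8927 | 0.7334 |

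**6. Allowing for the 20,000 CFU stage.** The article says only that carriage is not expected at 20,000 CFU, so its rate there has to be assumed. The probability of reaching 80,000 CFU is 1 minus the probability that 20,000 CFU is established under ≥4/9. With 50% carriage at 80,000 CFU:

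| Assumed carriage at 20,000 CFU | P(80,000 reached) | P(exactly 4/9 there), all trials |
|---|---|---|
| 0% | 1.0000 | 0.2344 |
| 10% | 0.9920 | 0.2344 × 0.9920 = 0.2325 |
| 20% | 0.9175 | 0.2344 × 0.9175 = 0.2150 |

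The lower stage changes the result little.

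**The case against.** The strongest reply is that the document already resolves the conflict. The Inoculation sentence is a summary, Figure 2 is named as decisive, and a team that follows Figure 2 acts correctly at 4/9. On that view 23.4% is the chance of landing on the one result where the wordings differ, not the chance of a wrong decision. That is right, and it limits the point to a correction of wording. It does not make the sentence correct: a decision threshold is still misstated in the section that staff would use.

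A related reply is that the sentence gives a sufficient condition, so it is silent at 4/9. Read strictly, that is so, and nothing in the article expressly sends a 4/9 result to 160,000 CFU. That step follows only if 4/9 is taken as insufficient. But a sentence offered as a summary of the stopping rule, naming a cut-off other than the rule's own, will be read as the rule.

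It can also be said that the documents do not prove which cut-off was meant, since the ≥50% question agrees with 5/9. This stands as a limit. The conclusion rests on the precedence that the article states, not on knowledge of intent.

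Finally, a question about a dose's true rate and the count used to answer it need not be the same number, and with nine participants a cut-off of 4/9 can reasonably serve a target of about 50%. That defends the rule, not the wording. As written, a dose with 4 carriers of 9 would be reported as answering yes to ≥50% colonisation on an observed 44.4%. The exact confidence interval planned for each dose would show the uncertainty (13.7% to 78.8% for 4/9), but it would not remove the mismatch.

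**Conclusion.** The concern holds. The Inoculation section misstates the rule that ends the study at 80,000 CFU, and the primary question is worded more strictly than the rule that answers it. The operative rule is ≥4/9, by the article's own references to Figure 2.

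The affected outcome is far from rare. It has probability 15.9% to 23.4% over true carriage of 60% down to 50%, given that 80,000 CFU is reached. Over all trials at 50% carriage it is 21.5% to 23.4%, if carriage at 20,000 CFU lies between 20% and 0%. These figures assume independent participants with a common carriage probability at each dose, and full cohorts of six and three challenged participants.

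The correction should be made but does not put the design in doubt, because following Figure 2 gives a definite decision at every count.

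**What to change.** Make two wording changes before any 80,000 CFU result is read:

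- In the Inoculation section, replace the cut-off of more than 4 from 9 with at least 4 of 9 participants, so that it agrees with the Figure 2 legend.
- Under Feasibility in the Statistical analysis section, reword the primary question along these lines: does one of the three doses give observed carriage of at least 4/9, the study's criterion for about 50% colonisation?

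Both are needed, since correcting only the Inoculation sentence leaves the ≥50% mismatch in place. The Study status section reports only eight participants inoculated, all at 20,000 CFU, so at submission there was still time to do this blind to the 80,000 CFU result.

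The change needs no extra participants, doses, stages or analyses. If the approved protocol carries the same wording, the Amendments section requires ethics committee and sponsor approval. The sponsor should confirm ≥4/9 when making the correction and state its known price: a dose with true carriage of 30% is accepted in 26.2% of trials, against 9.9% under ≥5/9. That price belongs to the rule already in force and is not caused by the rewording. If the sponsor in fact wanted 5/9, Figure 2 itself would have to change, which would be an amendment of the design.

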## Study protocol

### Study aims

The aims of this study are:

1. Establish controlled human infection with
*Streptococcus pneumoniae* serotype 6B in Malawi2. Confirm nasopharyngeal pneumococcal challenge dose required to establish ~50% carriage in Malawian participants3. Confirm safety and measure potential symptoms of controlled human infection procedures for study participants4. Confirm sampling protocols and laboratory assays for immunological assessment relevant to vaccine testing.5. Assess the feasibility and acceptability of consent and study procedures for participants.

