### Study status

At time of manuscript submission (23
^rd^ January 2020), the study has commenced recruitment and has currently inoculated eight participants at the 20,000 CFU dose

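### At exactly 4 carriers out of 9 on 80,000 CFU/naris, the inoculation text and Figure 2 disagree on whether the study ends, and 4/9 falls short of the 50% in the primary question

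*Protocol article*

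**What the plan says.** The carriage threshold appears in three places in the protocol article.

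- **Inoculation (dose escalation and sham inoculation):** "If 80,000 cfu/naris achieves more than 4 from 9 participants with carriage, then the study will end at that point". With nine inoculated, this means 5 or more.
- **Figure 2 legend:** "If the combined carriage rate of the completed cohorts is ≥4/9", the dose counts as established and the study concludes. The same algorithm restarts at 80,000 CFU/naris if 20,000 falls short. If 80,000 falls short, the study moves to 160,000 with 12 participants, 9 inoculated and 3 sham.
- **Statistical analysis, Feasibility:** the primary question is whether one of the doses will "lead to ≥50% nasal colonisation". To answer it, the Figure 2 algorithm "is followed and no statistical analysis is required".

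The paragraph on statistical significance gives Figure 2 the deciding role: "Success (feasibility) of the study will be decided according to the decision rules stated on" Figure 2. The target itself is looser elsewhere. Study aim 2 reads "Confirm nasopharyngeal pneumococcal challenge dose required to establish ~50% carriage in Malawian participants", and the Study hypothesis also gives an approximate 50%.

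**The concern.** The wordings part company at a single result, 4 carriers among 9. Figure 2 stops and names 80,000 as the dose. The Inoculation sentence's condition for ending is not met, so with Figure 2's own escalation clause the study would go on to 160,000. Nor do the thresholds line up with the primary question: 5/9 satisfies an observed rate of 50% or more, and 4/9 does not. The rule named as governing is thus the one that does not fit the question it is said to answer.

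At stake are the exposure of healthy volunteers to the highest dose, the dose carried into later vaccine studies, and whether feasibility is reported as achieved. If the threshold is not settled beforehand, it could be chosen once the count is known. The decision was still open at submission: the Study status section reports only "currently inoculated eight participants at the 20,000 CFU dose".

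**Working it through.** **Design figures first.** The maximum sample is (8 + 4) + (8 + 4) + 12 = 36, as stated under Recruitment target. The number of looks is 2 at least (20,000 passes both stages) and 5 at most (two at 20,000, two at 80,000, one at 160,000), as stated under Timing of analyses. The design is therefore being read as intended.

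**Inputs.** From the Figure 2 legend: 6 inoculated in the first stage, continue if at least 2 carry, then 3 more inoculated, and compare the total out of 9 with the threshold. The legend gives 50–60% carriage at 80,000 CFU from Liverpool. True rates of 30% and 40% are illustrative assumptions.

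**Observed rates.** 4/9 = 44.4%, exact 95% CI 13.7% to 78.8%. 5/9 = 55.6%, exact 95% CI 21.2% to 86.3%. No count out of 9 lies between these, so an observed rate of 50% or more requires 5/9.

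**Chance of the disputed count.** Let X6 ~ Bin(6, p) and X3 ~ Bin(3, p). Exactly 4 of 9 with the first stage passed can arise in three ways:

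- X6 = 2, X3 = 2: 15 × 3 = 45
- X6 = 3, X3 = 1: 20 × 3 = 60
- X6 = 4, X3 = 0: 15 × 1 = 15

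The total is 120, so P(exactly 4/9 after at least 2/6) = 120 p⁴(1 − p)⁵. At p = 0.5 this is 120/512 = 0.234.

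**Chance that the rule is met.** Five or more of 9 cannot occur with fewer than 2 of the first 6, so the stricter rule is P(Bin(9, p) ≥ 5); at p = 0.5 this is 256/512 = 0.500. The Figure 2 rule adds the disputed count: (256 + 120)/512 = 0.734.

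| True carriage | At least 4/9 (Figure 2) | More than 4/9 (Inoculation text) | Exactly 4/9 | 9 × P(exactly 4/9) |
|---|---|---|---|---|
| 30% | 0.262 | 0.099 | 0.163 | 1.5 |
| 40% | 0.505 | 0.267 | 0.239 | 2.1 |
| 50% | 0.734 | 0.500 | 0.234 | 2.1 |
| 60% | 0.893 | 0.733 | 0.159 | 1.4 |

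The last column is the expected number of 160,000 CFU/naris inoculations that depend on which wording is followed, given that the 80,000 dose is reached. The figures apply to the two-stage 20,000 and 80,000 cohorts, not to the 160,000 group, which enrols its 12 at once.

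**The case against.** The strongest reply is that the document already says which text governs. The Inoculation sentence is introduced as a brief summary, refers the reader to Figure 2, omits the first-stage rule, and states no action at exactly 4. The paragraph on statistical significance, the Feasibility paragraph and the Stopping criteria section all point to Figure 2. On that view the sentence is a slip, and the exposure figures arise only if the team follows the summary over the algorithm.

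Much of this stands. Figure 2 probably does govern, and non-stopping at 4/9 is an inference from the Inoculation sentence together with Figure 2's escalation clause. The probabilities above are chances of landing on the disputed count, not chances of a wrong decision. But the sentence cannot be dismissed as a plain slip, because its threshold is the only one that fits the 50%-or-more question.

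A second reply is that the question concerns the underlying rate, and a cut-off on nine people need not equal the target. That is fair, and the approximate 50% in the aims and hypothesis accommodates either threshold. However, the Feasibility paragraph says the algorithm alone answers the question. As an answer about the underlying rate it is weak: a dose with true carriage of 40% passes at least 4/9 in 51% of cohorts. The planned rates with exact intervals help the reader, but they do not remove the inconsistency.

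**Conclusion.** The concern holds. The rule that ends the study and decides the primary question has two thresholds, and the one that probably governs does not match the question as worded. The conflict is confined to 4/9, but that result has probability 0.159 to 0.234 over the 60% to 50% carriage the authors expect. At a true 50%, the choice of wording moves the chance of stopping at 80,000 between 0.734 and 0.500.

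These figures assume independent participants with a common carriage probability, and that the 80,000 dose is reached. Because Figure 2 is named as the deciding rule, this is a point to correct rather than a threat to the study. It should still be settled before the count is known.

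**What to change.** Use one threshold throughout, and keep at least 4 of 9. Figure 2 is the named rule, and the stricter version would fail a dose with true carriage of 50% in half of cohorts and send volunteers on to 160,000.

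- In the Inoculation section, change the condition to at least 4 of 9.
- In the Feasibility paragraph, replace the 50%-or-more criterion with the observed rule (at least 2 of 6, then at least 4 of 9), leaving approximately 50% as the target in the aims.
- Describe the established dose as the lowest tested dose that met the rule.
- Say that meeting the rule does not show true carriage of 50% or more, and that closeness to 50% is judged from the planned rate and its exact 95% interval.

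If an observed 50% or more is really intended, set Figure 2 to at least 5 of 9 instead and accept the lower pass rates in the table.

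Record the choice before the day 14 results of the 80,000 cohort are known. The cost is a few text edits, with the approval described under Amendments if the full protocol carries the same wording. Keeping at least 4 of 9 adds no participants.
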